#### Strategies to improve adherence to interventions

Our strategy to improve follow-up monitoring compliance includes face-to-face adherence reminders by the surgeon at regular postoperative follow-up visits. In addition, we will ask patients during the visit how best to contact them (e.g. phone, WeChat, text message). The method of reminding patients to attend follow-up visits to the questionnaire will depend on their preferred method of contact.

#### Provisions for post-trial care

There will be no provision and no compensation for patients who suffer harm as a result of their participation in the trial.

### Outcome measures

#### Primary outcome measures

The primary outcome measures are postoperative incision healing time and the time to return to normal activities, calculated in days (d) [20, 25]. The healing criteria are as follows: complete epithelialisation of the anal canal and perianal skin. The rectal mucosa should be intact, without ulcer or erosion.

Efficacy evaluation: Efficacy will be evaluated according to the efficacy evaluation for mixed haemorrhoids in the 2017 Standard for Diagnosis and Efficacy of TCM Diseases and Syndromes as follows: cured: the symptoms and haemorrhoids disappear; improved: the symptoms improve and the haemorrhoids shrink; and unhealed: there are no changes in symptoms and signs.

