#### Sample size

This study is a randomised controlled trial to evaluate modified ultrasound scalpel haemorrhoidectomy versus the Milligan-Morgan operation for mixed haemorrhoids. According to previous studies [19], the mean value of the experimental group is 10.50, the mean value of the control group is 13.40, and the standard deviation is 3.46 and 3.66, respectively. Two-sided tests is needed, with a test level of 0.05. Using the PASS 15.0 software, the sample size of the two groups is 33, and according to the 15% loss of follow-up, 78 subjects will be expected to be finally collected.

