#### Statistical analysis

This study is a randomised, single-blind, parallel controlled study. The primary endpoints are the time to incision healing and the time to return to normal activities after modified ultrasonic scalpel haemorrhoidectomy. It can be considered that the recovery time after the treatment of modified ultrasonic scalpel haemorrhoidectomy is approximately normally distributed when testing the superiority hypothesis of modified ultrasonic scalpel haemorrhoidectomy and conventional haemorrhoidectomy. The hypothesis of superiority will be tested in a one-tailed approach, with a *P* value of 0.025 or less considered to indicate statistical significance.

All analyses will be performed with R 4.3.2.

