#### Primary efficacy assessments

The primary efficacy measures in this trial are the time to postoperative wound healing and the time to return to normal activity. An equivalence test will be used, and the test hypothesis is as follows:

H0: the recovery time of the intervention group-the recovery time of the control group is ≤ 0;Hα: the recovery time of the intervention group-the recovery time of the control group is > 0.

The recovery time of the two groups will be calculated, and the 95% confidence interval (CI) of the difference between the two groups will be determined. The difference from baseline between the trial group and the control group can be approximated as following a normal distribution, and thus the efficacy analysis will be analysed with the use of T. The superiority hypothesis will be tested between the modified ultrasonic scalpel haemorrhoidectomy group and the conventional haemorrhoidectomy group, and the test *α* = 0.025 (one-sided test). If the *p* value is less than or equal to 0.025, the superiority of postoperative recovery time of the modified ultrasonic scalpel haemorrhoidectomy group compared with the conventional haemorrhoidectomy group will be verified.

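### Two primary endpoints share one one-sided 0.025, but the hypotheses and success statement cover only an undefined recovery time, and the sample size rests on one unnamed endpoint

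*Protocol article*

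**What the plan says.** **Endpoints.** Under Primary outcome measures: "The primary outcome measures are postoperative incision healing time and the time to return to normal activities", both in days. The Statistical analysis section repeats this: "The primary endpoints are the time to incision healing and the time to return to normal activities". Neither section ranks the two or says how they combine.

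**Threshold.** The same section says: "The hypothesis of superiority will be tested in a one-tailed approach, with a *P* value of 0.025 or less". One level is given, with no split.

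**Hypotheses and success.** Primary efficacy assessments opens by naming both endpoints. It then writes one null and one alternative, for *recovery time* only, and concludes that at p of 0.025 or below "the superiority of postoperative recovery time of the modified ultrasonic scalpel haemorrhoidectomy group compared with the conventional haemorrhoidectomy group will be verified".

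**Schedule.** Table 1 has one row for incision healing time and another for recovery time. No row is called return to normal activities.

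**Sample size.** "the mean value of the experimental group is 10.50, the mean value of the control group is 13.40", with SDs 3.46 and 3.66, and "Two-sided tests is needed, with a test level of 0.05". The result is 33 per group, or 78 in total after 15% loss. Endpoint, unit and power are not named.

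**A further measure.** Also under Primary outcome measures: "Efficacy will be evaluated according to the efficacy evaluation for mixed haemorrhoids", graded cured, improved or unhealed. It does not appear in the primary analysis.

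**The concern.** A reader cannot tell from these sections what would make the trial positive. Two endpoints are primary, one threshold is stated, and the decision rule is written for a term that may mean one of them or both. If healing time favours the new operation and return to activities does not, or the reverse, the text gives no answer. The sample size does not settle it, because the endpoint behind the two means is not named.

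What is at stake depends on the rule. If success on either endpoint counts, the false-positive rate exceeds the stated 2.5%. If both must succeed, the error rate is safe, but the trial has less power than the sample size calculation implies.

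**Working it through.** **1. Meaning of recovery time.** There are two readings.
- *It means return to normal activities.* Table 1 supports this: recovery time stands apart from incision healing time and is the only row that could hold the other primary endpoint. Then healing time, the first-named primary endpoint, has no written hypothesis or success rule.
- *It covers both endpoints.* The opening sentence of Primary efficacy assessments, which names both, supports this. Then both are tested and no rule covers a split result.

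The text is incomplete on either reading.

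**2. The plan's own sample size.** Inputs from the Sample size section:
- difference = 13.40 − 10.50 = 2.90
- common SD = √[(3.46² + 3.66²)/2] = √12.684 = 3.561
- two-sided 0.05, equal allocation, n = 33 per arm

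Noncentrality = 2.90 / (3.561 × √(2/33)) = 3.308. With 64 degrees of freedom the critical t is 1.998, and the noncentral t gives power 90.3%. Powers of 80%, 85% and 95% would need 25, 29 and 41 per arm, so 90% for one endpoint is the implied design. For dropout, 33/0.85 = 38.8, which rounds up to 39 per arm and 78 in total. The stated figures reproduce. Two-sided 0.05 and one-sided 0.025 give the same n here, so that difference in wording does not affect this point.

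**3. If either endpoint suffices, each tested at one-sided 0.025.** Error = 1 − P(Z1 < 1.96, Z2 < 1.96), bivariate normal with correlation ρ. For ρ = 0 this is 1 − 0.975² = 0.0494.

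**4. If both are required, each at one-sided 0.025.** Assume the same standardised effect on both, so each has power 0.903. For ρ = 0, joint power = 0.903² = 0.815. For other ρ it is the bivariate normal probability that both statistics cross, with each margin set at 0.903.

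| ρ (assumed) | Error, either suffices | Joint power, both required |
|---|---|---|
| 0 | 4.94% | 81.5% |
| 0.5 | 4.54% | 83.7% |
| 0.7 | 4.17% | 85.1% |

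The references are 2.5% error and 90.3% power for one endpoint. With a plain normal approximation for the margins, joint power is 83.0%, 85.0% and 86.3%; the gap is one of method.

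**5. If alpha were split equally.** At one-sided 0.0125, power per endpoint at 33 per arm is 84.2% under the same effect. Restoring 90% would need 39 evaluable per arm, and 39/0.85 = 45.9, so 46 per arm and 92 in total.

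**The case against.** **An analysis plan may settle this.** The article says that a statistical analysis plan was approved by the ethics committee, and that a full protocol is available on request. A multiplicity rule is often placed there. This stands in part: the article does not show that the sponsor is free to choose a reading after seeing results, and the analysing statisticians are to be blinded. It does not dispose of the point. The article itself commits to two primary endpoints, a level, hypotheses, a success statement and a sample size, and these do not fit together.

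**Stronger readings that a reader might infer.**
- *Each endpoint is given the full 0.025.* This is a natural inference, but it is not written endpoint by endpoint; one level is attached to one hypothesis pair.
- *There is no success rule.* There is one, for recovery time. What is missing is a rule covering both named endpoints.
- *The type I error is inflated.* Only if either endpoint suffices, which no section states. If recovery time means return to activities alone, one test is written and nothing is inflated.
- *The cured/improved/unhealed rating is a third primary test.* It appears under the primary heading with its own label, but no section gives it a hypothesis or any alpha, and the analysis sections do not call it an endpoint. It is misplaced and adds no error.
- *The sample size is wrong.* It reproduces for one endpoint.

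**The power figures are illustrative.** This stands. The 90% is inferred, and the documents give neither the second endpoint's effect nor the correlation.

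**Conclusion.** The point holds as a conflict within the protocol's own text: two primary endpoints and one undivided level, against hypotheses and a success statement for one undefined term and a sample size for one unnamed endpoint. Its size depends on which rule is meant. The one-sided error is about 4.2% to 4.9% against 2.5% if either endpoint suffices. Power is about 82% to 85% against an implied 90% if both are required. These ranges assume correlations between 0.7 and 0; the power range also assumes an equal standardised effect on both endpoints. The loss is moderate on either rule, and the stated sample size is sound for a single endpoint. This should be fixed, but it does not invalidate the design.

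**What to change.** 1. In Sample size, name the endpoint and unit that 10.50 and 13.40 describe, and state the power.
2. In Primary efficacy assessments, replace recovery time with a separate superiority hypothesis for each named endpoint. The alternative must point to shorter time. The present pair should not simply be copied: its alternative is intervention minus control above zero, which means a longer time with the new operation, and the section calls the test one of equivalence.
3. Test in fixed sequence at one-sided 0.025: first the endpoint used for the sample size, then the other only if the first succeeds. Both remain primary and the overall one-sided error stays at 2.5%.
4. List the cured/improved/unhealed rating with the secondary outcomes.

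Requiring both endpoints, or splitting alpha, would also remove the ambiguity, but at the loss of power shown in the working. The fixed sequence keeps about 90% power for the first endpoint at 33 evaluable per arm and needs no extra patients. Its price is that the second endpoint cannot be claimed if the first fails. The cost is wording in the protocol, the analysis plan and the registry entry. With recruitment reported as about two thirds complete, the change should be dated and made before any comparison by group.

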#### Secondary outcome measures

Postoperative complications: pain: A visual analogue scale (VAS) will be used in the two groups to observe the patients’ pain 4 h, 8 h, and 24 h after the operation and the pain from defecation for 7 consecutive days after the operation. Urinary retention will be assessed by the “with” and “without” method. Postoperative bleeding will be assessed as follows: 0 points: no bleeding; 1 point: blood on the paper; 2 points: drops of blood; 3 points: ejection of blood; and 4 points: massive bleeding that requires surgery to stop the bleeding. Postoperative oedema will be assessed as follows: 0 points: no oedema; 1 point: oedema in 1/4 of the anal margin incision; 2 points: oedema in 1/2 of the anal margin incision; 3 points: oedema in 3/4 of the anal margin incision; and 4 points: oedema around the perianal incision. Anal stenosis will be assessed by the “with” and “without” method.

Anal function evaluations 3 months and 6 months after operation: Anal function evaluation will be assessed by the CCF-FI as follows: (1) normal continence: the anus controls stool, and the passage of intestinal fluid and intestinal gas is normal; (2) partial anal incontinence: the anus cannot control intestinal fluid, intestinal gas, or loose stools; there is soiling of the underwear; or the anus has a sense of dampness; and (3) complete incontinence: the anus cannot control the passage of stool.

Evaluation of quality of life half a year after the operation: The simple SF-36 quality-of-life questionnaire (homemade) will be used to evaluate quality of life.

Evaluation of patient satisfaction rate half a year after the operation: The self-designed patient satisfaction questionnaire will be used, which is divided into very satisfied, satisfied, general, and no opinion, and calculates the percentages of the 4 levels.

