#### Recruitment and trial timeline

Researchers will recruit participants from the inpatient wards of the Department of Integrated Traditional Chinese and Western Medicine. After screening patients who meet the inclusion and exclusion criteria, the researcher will inform the participants of the different treatment methods available for their condition, provide information about the study, and have the participants sign a written informed consent form. A copy will be kept by the participant, and the original will be kept at the hospital. Considering the admission to haemorrhoid surgery in our hospital and the experience of the last 2 years, it is feasible to recruit the calculated patient sample size. Other strategies to increase recruitment include announcing the study on our hospital website and providing information in the waiting room of the hospital.

The participants who meet the criteria will be registered, their baseline data and clinical features will be collected before the operation, and measurements will be taken at each observation time node according to the CRF form after the operation (Table 1). Participants who met the withdrawal criteria shall strictly follow the criteria and provide records. The registration process, the intervention and evaluation schedule, and the study flow chart are shown in Table 1 and Fig. 1.

**Table 1 Tab1:** Schedule of the registration process, the intervention, and evaluations

Measures	Preoperative	Daily in-hospital study visits								Follow-up					
		POD 0	POD 1	POD 2	POD 3	POD 4	POD 5		POD ≥ 6	W 2		W 3	W 4	M 3	M 6
Incision healing time										X	X		X		
Recovery time										X	X		X		
Pain VAS		X	X	X	X	X	X	X		X	X		X		
Urinary retention		X	X	X	X	X	X	X							
Postoperative bleeding		X	X	X	X	X	X	X		X	X		X		
Postoperative oedema		X	X	X	X	X	X	X		X	X		X		
Anal stenosis	X	X	X	X	X	X	X	X		X	X		X	X	X
Cleveland incontinence score	X	X												X	X
SF-36	X	X													X
Satisfaction survey		X													X
Adverese events		X	X	X	X	X	X	X		X	X		X	X	X

*POD* Postoperative day, *W* Week, *M* Month, *VAS* Visual analogue score, *SF36* 36-Item short form health survey

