#### Discharge and follow-up

Wound healing and surgical complications will be observed 1, 2, 3, and 4 weeks after the operation.

Each participant will be followed up 12 and 24 weeks after the operation via WeChat, telephone, video, and outpatient clinics. At 3 months and 6 months after the operation, the Cleveland Clinic Florida Fecal Incontinence Score (CCF-FI) will be used to evaluate the anal condition of the patients and to evaluate whether the patients have postoperative anal incontinence. The simple SF-36 quality-of-life questionnaire (homemade) will be used to evaluate the patients half a year after the operation.

For the schedule of the trial, please see Table 1.

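### Continence is scheduled as a CCF-FI score with a preoperative value, but the outcome is defined as three categories with no score-to-category rule and no use of the preoperative value

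*Protocol article*

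**What the plan says.** Three places in the protocol article describe the continence measure.

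- **Recruitment and trial timeline, Table 1.** The row is labelled "Cleveland incontinence score". It is marked preoperatively and at months 3 and 6. A further early mark reads as POD 0, but the table columns are partly broken in the text, so nothing here rests on that mark. The text of the same section adds that "their baseline data and clinical features will be collected before the operation".
- **Discharge and follow-up.** At 3 and 6 months "the Cleveland Clinic Florida Fecal Incontinence Score (CCF-FI) will be used to evaluate the anal condition of the patients", with the further aim "to evaluate whether the patients have postoperative anal incontinence". The abbreviation list also expands CCF-FI as a score.
- **Secondary outcome measures.** The outcome is introduced as "Anal function evaluations 3 months and 6 months after operation" and defined by grade: "Anal function evaluation will be assessed by the CCF-FI as follows: (1) normal continence", then "2) partial anal incontinence: the anus cannot control intestinal fluid, intestinal gas, or loose stools" (soiled underwear and a damp feeling also count here), then "3) complete incontinence: the anus cannot control the passage of stool".

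The section on secondary efficacy assessments picks the test by data type. Measurement data get a t test or Wilcoxon test; ranked data get a Wilcoxon or CMH test.

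**The concern.** The schedule and the follow-up section point to a numeric score with a baseline. The outcome definition points to a three-level grade at two postoperative times. Nothing links the two. A reader cannot tell which variable is analysed, and because the test is chosen by data type, the test is not settled either.

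Two things are lost if the grades are analysed as defined. First, the middle grade spans everything from a damp feeling to loss of loose stool, so a patient who moves across that span is recorded as unchanged. Second, the definition makes no comparison with the preoperative state, so existing incontinence and incontinence arising after surgery are counted alike. The measurements needed to avoid both losses are already scheduled.

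**Working it through.** **Step 1: the three places side by side.**

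| Place | Form of the measure | Preoperative value | Score-to-category rule |
|---|---|---|---|
| Table 1 | score | marked | none |
| Discharge and follow-up | score, used to judge whether incontinence is present | not mentioned | none |
| Secondary outcome measures | three grades | not used | none |

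The document gives no continence rate, score distribution or power figure for this outcome, so there is no stated figure to reproduce. Everything below rests on assumed distributions. The only input from the document is 33 patients per group before loss to follow-up (Sample size section).

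**Step 2: rank-test efficiency of the grades relative to a score.** For a proportional-odds shift, the information in an ordered outcome with category shares p is proportional to 1 − Σp³. Assume a share p0 continent, p2 in the complete grade, and p1 = 1 − p0 − p2 in the partial grade. Under the score, spread p1 evenly over m levels.

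Relative efficiency = (1 − p0³ − p1³ − p2³) / (1 − p0³ − m(p1/m)³ − p2³)

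Example with p0 = 0.80, p1 = 0.19, p2 = 0.01, m = 5:
- Grades: 1 − 0.512 − 0.006859 − 0.000001 = 0.48114
- Score: 1 − 0.512 − 5 × 0.038³ − 0.000001 = 0.48772
- Ratio: 0.986

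| Continent (p0) | Complete (p2) | Ratio, m = 5 | Ratio, m = 10 |
|---|---|---|---|
| 0.90 | 0.01 | 0.997 | 0.997 |
| 0.80 | 0.01 | 0.986 | 0.986 |
| 0.70 | 0.01 | 0.964 | 0.963 |
| 0.60 | 0.02 | 0.933 | 0.931 |
| 0.50 | 0.02 | 0.878 | 0.875 |
| 0.30 | 0.02 | 0.686 | 0.679 |
| 0.20 | 0.02 | 0.532 | 0.524 |

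For this kind of shift, the grades keep nearly everything when most patients are continent, and about half when only 20% are.

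**Step 3: simulated Wilcoxon power at 33 per arm** (3,000 replicates, two-sided 0.05). Assumed score: 0 if continent, otherwise 1 plus a Poisson count capped at 18. Assumed grades: 0 is normal, 1 to 14 is partial, 15 or more is complete.

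| Difference between arms | Score | Grades |
|---|---|---|
| Share only: 20% vs 50% incontinent, Poisson mean 2 in both | 0.71 | 0.74 |
| Share and severity: 20% vs 50%, means 2 vs 4 | 0.87 | 0.75 |
| Severity only: 50% continent in both, means 2 vs 5 | 0.31 | 0.04 |
| Severity only: 30% continent in both, means 2 vs 5 | 0.74 | 0.05 |

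In the severity-only rows the grades reject at about the nominal error rate: the difference is invisible to them.

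**Step 4: rare incontinence.** With any incontinence in 5% vs 15% and scores uniform on 1 to 10 among those affected, power is 0.26 for the score and 0.29 for any against none. For 5% vs 20% it is 0.46 and 0.49. The score gains nothing here; power is low because events are few at 33 per arm.

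**The case against.** The strongest reply has four parts.

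- **The grades serve the stated purpose.** The follow-up section says the score is used to judge whether incontinence is present, and grades answer that. This is partly right, but it does not explain how a score becomes a grade, and a presence question needs the preoperative state if the incontinence is to be read as arising after surgery.
- **The score is still collected, and an analysis plan not shown could use it.** The score is indeed not thrown away. But the point is not a missing detail: the article states positively what the outcome is, and that statement does not match its own schedule.
- **Randomisation balances existing incontinence on average.** This stands. Leaving out the preoperative value costs precision and clarity of interpretation; it does not bias the comparison between arms.
- **A score would not rescue power if incontinence is rare.** This stands, as Step 4 shows.

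A reader might go further and infer that three grades discard most of the information, that this is the trial's main functional safety question, or that a finding of no difference is close to guaranteed. The document supports none of these. The information loss depends on an unstated distribution and is about 1% or less in Step 2 when 80% to 90% are continent. Anal function is listed as a secondary outcome, while safety is defined through adverse and serious adverse events. No equivalence or non-inferiority claim is made for continence, and low power with few events comes from the sample size, not from the grading. Nor does the usual variance saving from linear baseline adjustment carry over to a score that is mostly zero.

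**Conclusion.** The mismatch is real and can be checked from the document alone: a score with a preoperative value is scheduled, and a three-grade outcome with neither a mapping nor a baseline comparison is defined. Severity changes within the partial grade are invisible, and existing incontinence is not separated from incontinence arising after surgery.

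The statistical cost cannot be fixed from the document. Under the assumptions shown, it runs from nil (most patients continent, arms differing only in the share affected) to almost all power (0.31 or 0.74 falling to about 0.05 when arms differ only in severity). These figures rest on assumed score distributions and grade cut-offs and serve only as a range. This is a minor point on a secondary outcome, worth acting on because the correction costs so little.

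**What to change.** In the section on secondary outcome measures, name the CCF-FI score at months 3 and 6 as the analysed variable. Compare the arms with adjustment for the preoperative score, using a proportional-odds or rank-based method if most scores are zero. State the rule that maps the score to the three grades, and report the grades descriptively, cross-tabulated against the preoperative grade. Align the follow-up section and Table 1 with that wording.

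The cost is a change of wording and slightly more analysis work. No new visits or data are needed, since Table 1 already schedules the score. If incontinence turns out to be rare, the power gain will be small; the benefit is then mainly a clear definition and a visible baseline.

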**Fig. 1 Fig1:**
[figure not shown]
Flow chart of the research phases. VAS, visual analogue scale; SF-36, 36-Item Short Form Health Survey

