#### Secondary efficacy assessments

The statistical description and inference of the secondary indicators will be based on the characteristics of the data, and the appropriate descriptive indicators and hypothesis testing methods will be selected.

The comparison of general conditions between the two groups will be analysed by appropriate methods according to the type of indicators. The comparison between the groups of measurement data will be compared by the *t* test (homogeneity of variance, normal distribution) or the Wilcoxon rank sum test according to the distribution of data, and the chi-square test or exact probability method (if the chi-square test is not applicable) will be used for count data. The Wilcoxon rank sum test or stratified chi-square test (CMH test) will used for ranked data. Data analyses will be performed by statisticians who are independent of the study team and who are blinded to the group assignments. The acceptable significance level for all analyses will be *P* < 0.05.

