## Abbreviations

PPH: PROXIMATE® PPH haemorrhoidal circular stapler haemorrhoidopexy
RPH: Automatic haemorrhoid ligation
FEH: Ferguson’s with electrosurgical haemorrhoidectomy
AEs: Adverse events
SAEs: Serious adverse events
VAS: Visual analogue score
SF-36: 36-Item Short Form Health Survey
CCF-FI: Cleveland Clinic Florida Fecal Incontinence Score
CRF: Case report form

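### The 6-month quality-of-life instrument is described both as a study-made form and as the 36-Item Short Form Health Survey, and no use of its scheduled preoperative score is stated

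*Protocol article*

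**What the plan says.** The protocol article names the quality-of-life instrument in five places.

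- Secondary outcome measures: "The simple SF-36 quality-of-life questionnaire (homemade) will be used to evaluate quality of life", introduced as "Evaluation of quality of life half a year after the operation".
- Discharge and follow-up: "The simple SF-36 quality-of-life questionnaire (homemade) will be used to evaluate the patients half a year after the operation".
- Table 1 (Recruitment and trial timeline) has a row labelled SF-36, and its footnote expands the label as "36-Item short form health survey".
- The Fig. 1 legend: "SF-36, 36-Item Short Form Health Survey".
- Abbreviations: "SF-36: 36-Item Short Form Health Survey".

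On timing, the two text sections name only the half-year assessment. The SF-36 row of Table 1, as extracted, carries marks at Preoperative, POD 0 and M 6. The text above the table adds that "their baseline data and clinical features will be collected before the operation".

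On analysis, Secondary efficacy assessments first says that methods will be chosen to suit the data. It then gives rules by data type. The sentence beginning "The comparison between the groups of measurement data will be compared by the" goes on to name the t test or, depending on the distribution, the Wilcoxon rank sum test. Neither a covariate nor a change score is mentioned.

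**The concern.** The instrument is part of the definition of an outcome. Quality of life at 6 months is listed in the abstract and in the objectives, so it is a stated efficacy outcome and not a background measurement. When the text calls the form simple and homemade while the table, figure and abbreviation list call it a standard published survey, a reader cannot tell what a 6-month score will mean. If the form is study-made and the label stays, a difference between the operations, or the lack of one, could be read on the SF-36 scale and set beside other trials without justification. If the standard form is in use, readers will discount a sound result because the text calls it homemade.

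The second part is about efficiency. A preoperative score appears in the schedule, yet the article gives it no role, and the tests named for measurement data would leave it out. In a trial of 39 per group, a baseline that has already been collected is the cheapest source of precision.

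**Working it through.** **1. Which instrument?** Set side by side:

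| Place | Identity given |
|---|---|
| Secondary outcome measures | simple, homemade form carrying the SF-36 name |
| Discharge and follow-up | the same |
| Table 1 footnote | 36-item survey |
| Fig. 1 legend | 36-item survey |
| Abbreviations | 36-item survey |

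The homemade description occurs twice, in separate sections, so a single slip of the pen is unlikely. The satisfaction questionnaire is also described as self-designed in Secondary outcome measures, so this trial does use study-built forms. Neither fact proves that the quality-of-life form is study-built.

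**2. When is it measured?** Text: half a year only. Table 1: Preoperative, POD 0 and M 6. The extracted header has blank columns between POD 5 and POD ≥ 6 and between W 2 and W 3, so marks further right may be displaced. The Preoperative column lies to the left of both blanks. The POD 0 mark has no counterpart in the text.

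**3. What would the preoperative score be worth?** The article gives no power statement, standard deviation or expected effect for quality of life, so there is no figure on this outcome to reproduce.

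The number per arm comes from Sample size, which concerns a different endpoint: 33 per group, 15% loss, 78 in total. That figure reproduces if 90% power is assumed, since the power is not stated. The difference is 13.40 − 10.50 = 2.90, and the SD is √((3.46² + 3.66²)/2) = 3.561. The two-sided 0.05 t-based calculation gives 32.7, hence 33 per group. Then 33/0.85 = 38.8, hence 39 per group and 78 in total.

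Assumptions, none taken from the documents: correlation r between preoperative and 6-month scores of 0.4 to 0.6, a true effect of 0.5 SD, and a single continuous score.

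- Adjusting for baseline multiplies the variance of the group comparison by 1 − r².
- Effective standardised effect = 0.5/√(1 − r²).
- Noncentrality = effective effect × √(33/2).
- Power is from the noncentral t distribution, two-sided α = 0.05, 33 per arm. The one degree of freedom spent on the covariate is ignored.

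| r | 1 − r² | Effective effect | Noncentrality | Power |
|---|---|---|---|---|
| unadjusted | 1.00 | 0.500 | 2.03 | 51.6% |
| 0.4 | 0.84 | 0.546 | 2.22 | 58.8% |
| 0.5 | 0.75 | 0.577 | 2.35 | 63.7% |
| 0.6 | 0.64 | 0.625 | 2.54 | 70.6% |

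The variance reduction is therefore 16% at r = 0.4 and 36% at r = 0.6.

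**The case against.** The strongest reply is that only the naming conflict is on the page. Secondary efficacy assessments leaves the choice of method open. The sentence naming the t test and Wilcoxon test follows one about comparing general conditions, and it never mentions quality of life. The section on communicating amendments refers to a statistical analysis plan that is not shown, and covariate adjustment of a secondary outcome commonly belongs there. All of this stands. A reader might infer that the preoperative score is discarded, but the article does not say so. What can be said is that no use is stated and that the tests named for measurement data do not use it.

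A reader might also infer that the quality-of-life result cannot be an SF-36 result at all, or that the form lacks scoring and norms. That too goes beyond the text. The questionnaire is not reproduced, and the word homemade could be a translation slip or mean a locally prepared version. The limit on SF-36 claims follows only if the form is in fact study-made. Nor does the article announce domain scores, comparison with norms or comparison across trials, so misreporting is a risk and not a stated plan.

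Finally, the power figures rest on assumed correlations and an assumed effect, and they do not measure the labelling problem. That is correct. They show only what adjustment could be worth. The table marks also come from an imperfect extraction, which matters more for POD 0 than for the Preoperative column.

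**Conclusion.** The article contradicts itself on the identity of its quality-of-life instrument, and the five places must be reconciled. What the trial may claim depends on the answer: SF-36 scores if the standard form is used, scores on a study-specific questionnaire if not. The size of this problem cannot be computed from the document.

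A preoperative score is scheduled without a stated use. Adjusting for it is a better choice than the unadjusted tests named, provided the outcome is analysed as a continuous score. The gain shown in the working holds only under the assumed correlation range and the illustrative effect, with 33 per arm analysed.

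This is a secondary outcome. The change is worth making because it costs little and determines how a published result may be read.

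**What to change.** - **If the form is study-made:** keep it, since recruitment is about two thirds complete (Trial status) and a switch would leave earlier participants without a matching baseline. Call it a study-specific questionnaire in the text, Table 1, the Fig. 1 legend and the abbreviations. Make no SF-36 domain, norm or cross-trial claim.
- **If it is the standard 36-item form:** remove the words simple and homemade from Secondary outcome measures and Discharge and follow-up.
- **Timing:** state the preoperative and 6-month assessments in the outcome text, and say whether the POD 0 mark in Table 1 is a real assessment or a table error.
- **Analysis:** if the score is continuous, specify before analysis that groups are compared at 6 months by ANCOVA with the preoperative score as covariate, reporting the adjusted difference and its 95% confidence interval. If the statistical analysis plan already says so, one line in the article is enough.

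Cost: a wording correction and one line of analysis. No new data are needed if the preoperative scores have been collected as Table 1 schedules.
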